(i) Taurine, a conditionally essential amino acid, is not used by the body for protein synthesis and exists in high concentrations in energy-demanding organs such as the brain, retina, heart, and skeletal muscles. Its abundance invariably reduces as animals and humans age (1). A recent multinational study found that taurine supplementation increased lifespan in middle-aged mice by 10-12% and health span (including a lower fat mass, better bone density, reductions in fasting blood sugar and mitochondrial and DNA damage) in older nonhuman primates (equivalent to 45-year-old humans) compared to control animals. Taurine improves cellular and organ function in multiple ways and has been labelled as one of the 'Longevity amino acids' (2). A meta-analysis showed that taurine supplementation could reduce glycated haemoglobin (HbA1c) level by 0.4% (3); but the validity of this result was limited by small number of patients (N=209 from five trials), short supplementation duration (<16 weeks) and, most importantly, the largest randomised-controlled-trial (RCT) (n=63) had a high-risk of bias in random-sequence generation and allocation concealment (3). Another subsequent RCT (N=120) in diabetic patients showed that taurine supplementation (1g/day x 8 weeks) resulted in lower serum insulin levels, Homeostatic-Model-Assessment-of-Insulin-Resistance, and biomarkers of endothelial dysfunction but not HbA1c, likely related to the short duration of supplementation relative to the long half-life of HbA1c (4).

(ii) Reducing healthcare burden is paramount as the Hong Kong population is rapidly ageing. Currently, many professional nutritional guidelines have largely focused on macronutrients. Recent studies have revealed the importance of nutritional elements in promoting healthy ageing (2). **An adequately-powered RCT with sufficient duration of supplementation is essential to confirm whether taurine can promote healthy ageing.** If it is proven to be effective, this trial will change international nutritional guidelines and public health policies, reduce healthcare utilisation, and improve quality of life for the community at large. Conversely, if the results are negative (despite adequate statistical power and duration of supplementation), taurine supplementation should not be used by the public, reducing society's unnecessary expenditure on an ineffectual therapy.

b(ii). **Introduction:**

Ageing population is an important issue around the world including Hong Kong. The proportion of elderly persons aged ≥65 in Hong Kong rose from 13% in 2011 to 20% in 2021; median age of the population increased from 41.7 to 46.3 years during the same period. Furthermore, an increasing number of people are frail with comorbidities affecting their quality of life and increasing burden on the healthcare system. Recent research suggested that frailty and many chronic health conditions are pathogenically linked to 'accelerated biological ageing' (5) caused by DNA-methylation, spontaneous somatic mutations such as Clonal-Haematopoiesis of Indeterminate-Potential, mitochondrial dysfunction, endoplasmic reticulum (ER) stress, and accumulation of advanced-glycation-end-products (AGEs) (6-8).

Exercise has consistently been shown to improve human health including ageing-related cognitive decline (9) and frailty (10). A combination of exercise with a nutritional intervention between 1 and 12 months has been shown to reduce biological age (11-13). However, in the secondary analysis of a factorial-designed RCT over a 12-month period, diet alone could decrease biological age more than

exercise alone (-2.4 vs -0.2 years,  $p < 0.05$ ) (13). A recent systematic review also showed that combining exercise with hypocaloric diet did not further improve glycaemic control in obese diabetic adults (14), suggesting some micronutrients may be critical in promoting healthy ageing (2).

Taurine (2-aminoethanesulfonic acid) is essential in infants because its deficiency may hinder brain development (15). Human milk contains taurine and formula milk is supplemented with taurine to compensate for insufficient endogenous taurine synthesis. In adults, the primary source of taurine is the diet, especially seafood and dark meat, with an intake seldom exceeds 400mg/day. Interestingly, blood taurine levels can be increased after exercise (1); with some authors suggested that taurine may play a part to mediate the metabolic health benefits of exercise (1,16).

The mechanisms through which taurine may improve health have been summarised in our recent review (17), and by others (18). In brief, taurine supplementation improves mitochondrial and ER function, pancreatic  $\beta$ -cells survival, bone, retinal and mental health in animal studies. In small human studies, taurine improves glycaemic control, exercise capacity, and myocardial function. Taurine interacts with gut microbiome, increases bile acid conjugation (19), stimulates glucagon-like-peptide-1 (GLP-1) secretion, and inhibits sodium-glucose-transporter-1 (SGLT-1) non-competitively (with 80% reductions in  $V_{max}$  and Michaelis-Menten-constant for glucose) (20-24). Gut microbiome and bile acids are key mediators of cardiometabolic health (25,26) while SGLT-1 inhibition reduces glucose absorption (24) and postprandial hyperglycaemia (27). Taurine is also a reactive-carbonyl-species (RCSs) scavenger (through a competitive Schiff-base reaction) (28) and can reduce haemoglobin glycation (29) and plasma AGEs — as demonstrated in a small RCT (30).

In summary, despite the strong experimental evidence supportive of taurine's health benefits, high-quality human data does not exist. Taurine is synthesized commercially in a pure form (hence also suitable for the vegans), inexpensive (<US\$1/g), and considered safe for human consumption at a dose <6g/day by the European Food Safety Authority (31). There is an urgent need to identify innovative ways to improve human health span (and not just lifespan) by minimising accelerated biological ageing (32). Before an adequately powered RCT assessing the effectiveness of taurine in improving long-term human health is conducted, a high-quality phase II trial assessing the medium-term metabolic benefits of taurine supplementation is need.

**c. Aims and Hypotheses to be Tested:**

We aim to determine whether compared to placebo, oral taurine supplementation (3g/day for 6 months) will

- (a) improve glucose metabolism resulting in reduced HbA1c among adult healthcare workers,
- (b) improve blood low-density-lipoprotein (LDL) and triglyceride levels, biological age — as measured by the PhenoAge model (32) — and accumulation of AGEs; and
- (c).

We hypothesize that taurine supplementation will:

1. improve glucose metabolism resulting in reduction in HbA1c; and
2. reduce biological age, and LDL and triglyceride, and AGEs levels

d. **Plan of Investigation:**

(i) Study design

The proposed study is a parallel-arm design, superiority, double-blinded, stratified phase II Bayesian Optimized RCT. Our proposed RCT aims to overcome the existing studies limitation, and to confirm the mechanisms through which taurine could exert its health benefit., as described in our recent review (17).

(ii) Methods

After obtaining written informed consent, healthcare worker participants will be randomly allocated to receive either oral taurine or identical-looking capsules daily for a 6-month period with 1:1 allocation ratio using computer-generated sequence (with variable block sizes), stratified by' chronological age ( $\leq 45$  vs  $>45$ -year-old) and pre-existing diabetic status. Exclusion criteria include those who: (a) are taking taurine prior to enrolment, have (b) chronic renal disease (eGFR $<30$ ml/min: as taurine can accumulate in renal failure) (35), (c) insulin-dependent diabetes mellitus, (d) a bleeding disorder (e.g. platelet count  $<100 \times 10^9/L$  or treated with dual antiplatelet agents: as taurine has potential antiplatelet activity in vitro) (36), (e) received active chemo/immunotherapy  $<30$  days before enrolment or likely to receive such treatment during the study, or (f) are pregnant or planning to become pregnant.

We will use taurine capsules produced by Optima Ovest, the company from the Western Australia. The placebo is a proprietary product from Colorcon called StarCap. These capsules will be stored in our research office. Participants will be given the bottles of study capsules as allocated once enrolled. REDCap database will be used for randomization, treatment allocation, and data collection.

**Intervention:** Identical-looking placebo or taurine (1000mg capsule x3 orally in one sitting per day) is the study intervention - a dose is higher than that from standard daily dietary intake (37), well within the safe recommended dose (31), and similar to the (equivalent) dose used in the recent nonhuman primate study (1). Significant side effects were not reported in previous human RCTs using similar doses (3,4,30). Participants will be advised to take the study capsules in the morning but taking it at other times is also allowed. At the end of study, unused study capsules will be counted to assess compliance. The participants will be allowed to continue with their normal diet and usual medications but will be advised to take the study capsules one hour apart from their usual medications, even though significant interactions between taurine and commonly used medications have not been reported.

**Primary outcome:** Difference in the proportion of patients who have a reduced HbA1c concentration comparing 6-month to baseline between the two treatment groups.

**Secondary outcomes:** Difference in the changes from baseline to 6-month follow-up between the two groups in (a) LDL and triglyceride levels, (b) PhenoAge (32), (c) body weight, (d) International Physical Activity Questionnaire (IPAQ)(**Appendix 1**) (38), (e) Center for Epidemiologic Studies Depression Scale (CES-D)(**Appendix 2**) (39), (f) systolic and diastolic blood pressure, (g) AGEs index (measured non-invasively using the skin autofluorescence technology) (40), insulin and HOMA-IR, and Brain-derived neurotrophic factor (BDNF) levels.

**Tertiary outcome: microbiome sub-study** - Eighty participants will be invited to participate in a

sub-study (40/group). Faecal samples at baseline and at 6-month follow-up will be obtained and their gut microbiome between the two groups, as well as between baseline and at 6-month follow-up, will be compared including the differences in gut microbiota diversity in relation to changes in plasma taurine (19), and methylglyoxal (a major precursor of AGEs) (8,30) levels.

- (iii) Subjects (with justification on the sample size) Having a healthy healthcare workforce is paramount in achieving a sustainable healthcare system as noted in many countries during the COVID-19 pandemic. This RCT will be conducted primarily in healthcare workers at the New Territories East Cluster of Hospitals including Prince of Wales Hospital, North District Hospital and Alice Ho Miu Ling Nethersole Hospital. Poster will be posted in these hospitals for promotion purpose. As healthcare workers are intrinsically interested in maintaining their health, they are likely to adhere to the study protocol. All healthcare-related workers who can read and understand written English or Chinese translated version of the study questionnaires will be invited to participate, including doctors, nurses, physiotherapists, dietitians, or research-related workers. Our sample size is based on the primary outcome – difference proportion of participants with a reduced HbA1c at 6-month compared to baseline between the two groups using a parallel design with 1:1 allocation.. Taurine was previously shown to reduce HbA1c by 0.41% (95%CI 0.09-0.74; p=0.001) (3). In this BOP2 trial, conditions for the stopping for superiority or futility will be based on absence of an informative prior, HbA1c concentrations will be reduced after 6-month of study intervention in the experimental and the control groups in 40% and 10% (possibly due to Hawthorne effect), respectively. The margin of meaningful difference between the two groups is set at 10%. Assuming one-sided type I error of 10% is acceptable to prove superiority or futility, this trial will have 80% with a total sample size of 80. Three interim analyses after enrolling 20, 40 and 60 participants will be performed to facilitate the BOP2 technique (Appendix 3). .

- (iv) Data processing and analysis

**Data Collection:** We will record participants' age, weight, height, comorbidities, usual medications, and dietary restrictions. In addition to testing for HbA1c, LDL and triglyceride concentrations, the following fasting blood tests - albumin, creatinine, C-reactive protein, lymphocyte percentage, red blood cell distribution width, mean cell volume, white blood cell count, alkaline phosphatase, glucose (to compute the PhenoAge) (32), taurine, tauroursodeoxycholic, insulin, BDNF, and methylglyoxal levels - will be obtained at baseline and 6-month. The participants will be advised to take the study capsules in the morning between 1 and 3 hours prior to the 6-month follow up blood tests. Taurine, tauroursodeoxycholic, insulin, BDNF, and methylglyoxal levels will be analysed by the ELISA assays. For the microbiome sub-study, stool samples are aliquoted into cell culture cryogenic tubes and immediately stored at -80°C for metagenomic sequencing locally.

**Data analysis:** Continuous variables will be reported as mean (SD) or median (interquartile range). Mann-Whitney test (or t-test when appropriate), including 95% confidence interval for differences between groups, will be used to analyse the outcomes. Shotgun metagenomic sequencing and paired comparisons will be conducted when comparing baseline and 6-month follow-up microbiome genus- and species-level abundance data, and whether any changes are related to the plasma taurine and methylglyoxal levels.

A subgroup analysis by excluding participants allocated to the taurine group who have 6-month plasma taurine levels less than the mean plasma taurine level of the control group, suggestive of

non-compliance to the study intervention, will be conducted. A one-sided p-value  $<0.10$  without Bonferroni adjustment will be taken as significant for the primary outcome in this phase II trial. Continuous outcome measures will be analyzed by analysis of covariance (ANCOVA) (while adjusting for baseline data), and a p-value  $<0.05$  without Bonferroni adjustment will be considered significant for these secondary outcome measures. Furthermore, the associations among these continuous outcome measures will be explored to advance our understanding of the mechanisms underlying accelerated biological aging.

(v) Potential pitfalls and contingency plans

**Safety and tolerability:** A two-member independent data safety monitoring committee (DSMC) will be formed prior to ethics application. Previous human taurine RCT did not report significant increases in adverse events (AEs) (3,4,30). A pre-plan safety margin is set to un-blind the results to the DSMC should the relative risk of AEs is  $>3$ . If the AE rate is in favour of the control group, the trial will be ceased. The reportable AEs include (a) gastrointestinal upset requiring medical attention or cessation of the study capsules, (b) allergic skin rashes, (c) spontaneous hypoglycaemia ( $<4\text{mmol/L}$ ), (d) unexpected bleeding from any sites after commencement of study capsules, and (e) new symptoms the participants believe are related to the study medications resulting in cessation of study capsules.

The placebo capsules contain high-purity, spray-dried, National Formulary standard, lactose monohydrate, a purified form of milk sugar and free of milk protein. It is an inactive substance that commonly used as a placebo filler due to its characteristics of stability, compressibility and neutral taste. It is recorded as a generally recognized as safe (GRAS) food substance in the U.S. Food and Drug Administration (41). Research shows that people with lactose intolerance are able to intake up to 12 grams of lactose with only mild symptoms or even no symptoms (42).

**Funding** This Phase II trial is internally funded by the Department of Anaesthesia and Intensive Care, the Prince of Wales Hospital and the Chinese University of Hong Kong.

**Ethical considerations:** Before obtaining written informed consent, the purpose of the study, procedures, risks and benefits of participation, and the time commitment involved will be explained to eligible patients by study research staff. Participants will also be informed that benefits from taking taurine remain scientifically unproven, and results may vary from person to person. Patients may withdraw from the study without prejudice at any time during the study. Data will be kept confidential in secure offices of the Department of Anaesthesia and Intensive Care for seven years. Only group data will be published. Approval for the project will be obtained from The Joint Chinese University of Hong Kong-New Territories East Cluster Clinical Research Ethics Committee. The study will adhere to local laws, Declaration of Helsinki, ICH-GCP and institutional policies. Participants will be able to obtain all the blood test results including their estimated biological age, and their group allocation at the end of the study. Considering the travel expense participants need, transportation reimbursement (up to HK\$100) will be issued to participants who require transportation to the study centre. No other financial incentives or compensation will be provided to the participants.

e. **Key References:**

2. Ames BN. Prolonging healthy aging: Longevity vitamins and proteins. *Proc Natl Acad Sci U S A* 2018;115(43):10836-10844. doi: 10.1073/pnas.1809045115.

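### The sample size rests on a BOP2 rule with a 10-point margin, but the analysis section judges the primary outcome by a one-sided p<0.10 tied to neither the margin nor the BOP2 boundaries, and the protocol does not say which rule decides

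*Protocol*

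**What the plan says.** The primary outcome is binary: "Difference in the proportion of patients who have a reduced HbA1c concentration comparing 6-month to baseline between the two treatment groups" (Primary outcome, section d(ii)).

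Section d(iii), on sample size, describes a BOP2 trial that may stop for superiority or for futility, with no informative prior. Reduced HbA1c is expected "in the experimental and the control groups in 40% and 10% (possibly due to Hawthorne effect), respectively". It adds: "The margin of meaningful difference between the two groups is set at 10" (per cent). The error rate is given as "Assuming one-sided type I error of 10% is acceptable to prove superiority or futility", and the result as "this trial will have 80% with a total sample size of 80". The word power is missing from that sentence, and I take it to be meant. On monitoring: "Three interim analyses after enrolling 20, 40 and 60 participants will be performed to facilitate the BOP2 technique", with a reference to Appendix 3.

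Section d(iv), Data analysis, gives the only explicit significance criterion for the primary outcome. A one-sided p-value below 0.10 "without Bonferroni adjustment will be taken as significant for the primary outcome in this phase II trial". That paragraph does not mention the margin, a posterior probability, BOP2 or the interim looks. It names no null hypothesis for the p-value.

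**The concern.** The two sections agree on a one-sided 10% level but not on what has to be shown. Section d(iii) asks for evidence that the difference in responder proportions exceeds 10 points. Section d(iv), read as most analysts would read an unqualified superiority p-value, asks only for evidence that the difference exceeds zero. These are different hurdles, and the sample size was derived from the higher one.

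What is at stake is the trial's verdict. A range of plausible results would count as success under one section and failure under the other, and no sentence settles which prevails. If this stays open, the choice could be made after the data are seen. The quoted power and error rate would then not describe the rule actually applied.

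**Working it through.** **Inputs, all from section d(iii):** taurine 40%, placebo 10%, margin 10 points, one-sided 10%, 80 participants at 1:1 (40 per arm), looks at 20, 40, 60 and a final look at 80. The normal quantiles are 1.2816 for one-sided 10% and 0.8416 for 80% power.

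**1. Reproducing the stated 80%, against the margin.** Unpooled z-test, single look:

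- standard error = √[(0.4×0.6 + 0.1×0.9)/40] = √(0.33/40) = 0.0908
- (0.30 − 0.10)/0.0908 − 1.2816 = 2.202 − 1.282 = 0.920, so power = 82%
- n per arm for 80% = 0.33 × (1.2816 + 0.8416)²/0.20² = 37.2, so 38 per arm, 76 in total

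Other margin-based versions give nearly the same power:

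| Margin rule | Power at 40% v 10% |
|---|---|
| Single look, posterior P(difference > 10 points) > 0.90, Beta(1,1) priors, exact | 79% |
| The same with Beta(0.5,0.5) priors | 81% |
| BOP2-type, futility looks at 20/40/60, tuned to at most 10% error at 20% v 10% (error obtained 9.5%) | 81% |
| O'Brien-Fleming-type superiority stopping over four looks (error obtained 9.7%) | 81% |

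The stated 80% is therefore sound if success means exceeding the 10-point margin.

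**2. The same inputs against zero difference.** Pooled proportion 0.25:

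- null standard error = √(2 × 0.25 × 0.75/40) = 0.0968
- (0.30 − 1.2816 × 0.0968)/0.0908 = 1.937, so power = 97%
- exact power of the pooled z (chi-square) test = 97.7%; Fisher's exact test 96%
- n per arm for 80% = (1.2816 × √0.375 + 0.8416 × √0.33)²/0.30² = 17.9, so 18 per arm

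A p<0.10 rule against zero would have needed 36 participants for 80% power, not 80.

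**3. Where the verdicts part.** Take 4/40 placebo responders, the expected number, and one final look:

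| Taurine responders | Observed difference | One-sided p against zero (pooled z) | Posterior P(difference > 10 points), Beta(1,1) |
|---|---|---|---|
| 8/40 | 10.0 points | 0.105 | 0.47 |
| 9/40 | 12.5 points | 0.065 | 0.59 |
| 12/40 | 20.0 points | 0.013 | 0.85 |
| 13/40 | 22.5 points | 0.007 | 0.91 |

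From 9 to 12 taurine responders, p<0.10 is met and the margin rule (posterior above 0.90) is not. Fisher's test would start at 10/40.

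**4. Behaviour when the true difference only equals the margin (20% v 10%).** The pooled test at p<0.10 succeeds 49% of the time (Fisher 38%). The single-look margin rule succeeds 8% of the time (9% with Beta(0.5,0.5) priors), and the tuned BOP2-type rule 9.5%.

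**5. A caution only.** If an unadjusted p<0.10 against zero were also used for superiority at each of the four looks, simulation gives a type I error of 22% (10% v 10%) to 24% (40% v 40%). The protocol does not state that procedure.

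**The case against.** The strongest reply is that section d(iv) names no null hypothesis. It uses the same one-sided 10% level as section d(iii), and if its p-value is taken against the 10-point margin with boundaries set for the looks, the two sections agree and the 80% stands. That is correct, so the rules conflict only on the ordinary reading of a superiority p-value. It does not remove the point, because no sentence asks for the margin reading.

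Appendix 3, and perhaps a separate analysis plan, may hold the cut-offs. They may well do so, but cut-offs held there would not by themselves say what the separate criterion in section d(iv) is for. The margin-based power stays at 79–82% across every version tried, so the comparison does not hang on one assumed set of priors or boundaries.

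Two stronger readings are tempting and should not be drawn:

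- A reader might infer that the missing Bonferroni adjustment means the four looks go uncorrected and the error rate is more than doubled. The same phrase is used in that paragraph for the secondary outcomes, where it plainly concerns multiple endpoints. Section d(iii) gives interim stopping to BOP2. The 22–24% figure therefore belongs to a procedure the protocol does not describe.
- A reader might infer that p<0.10 accepts observed differences the protocol calls too small to matter. With 40 per arm, the pooled test requires an observed difference of at least 10 points for every placebo count from 2 to 19. It passes below that only at 0 or 1 placebo responders, when 4 are expected. What the p-value rule lacks is adequate evidence that the true difference exceeds the margin, which is a narrower complaint.

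It is also fair to say that 80 participants are enough under either rule if the 40% v 10% assumption holds.

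**Conclusion.** The point stands in this form: the protocol sizes the trial on one rule and states a significance criterion that is not tied to it, without saying which decides. The 80% figure is not wrong; it belongs to the margin rule. Read as an ordinary test against zero, the criterion in section d(iv) has about 97–98% power instead of 80%. With 4/40 placebo responders it is met with four fewer taurine responders (9 v 13 of 40), and at a true 10-point difference it succeeds about 49% of the time against about 8–10%.

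This rests on three assumptions. The p-value is taken against zero difference, which the text neither states nor excludes. The priors (Beta(1,1) or Beta(0.5,0.5)), the posterior cut-off of 0.90 and the tuned BOP2-type boundaries are mine, because Appendix 3 is not shown. Error for the margin rule is calibrated at 20% v 10%, that is, at the expected placebo rate plus the margin. The document does not support a claim that the two rules cannot be reconciled, nor one that the stated error rate is already inflated by the looks.

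**What to change.** State one primary decision rule: success if the posterior probability that the taurine-minus-placebo difference in responder proportions exceeds 10 points passes the BOP2 cut-off for that look. Set the cut-offs so that total one-sided error over all four looks, counting any superiority stop, is 10% at a true 10-point difference.

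Then do one of two things with the p-value in section d(iv): label it descriptive, or state that it is tested against the 10-point margin using those same boundaries. Say in section d(iii) that the 80% is power against that margin, and restore the missing word.

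The cost is a protocol wording change and a check of the existing BOP2 calculation. No participants are added. It should be done before the first interim look, so that the rule is fixed before any comparative data are seen.
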